### Novelty

Our protocol is designed to address this by incorporating active LV unloading strategies under prespecified criteria (see below). Early active LV unloading during ECMO support improves survival in patients with cardiogenic shock, and concomitant LV unloading has been associated with favorable outcomes in refractory cardiac arrest. We incorporate the concept into the ECPR to validate its efficacy. The estimated call to ECMO perfusion may be expected longer than previous studies since we allowed emergency call to ED within 60 min.

## Study design

This is an investigator-initiated, multicenter, open-label, interventional randomized clinical trial. The responsible investigator is the **Taipei Metro Out-of-Hospital Cardiac Arrest Total Care**
*Consortium.*

The trial has been registered on ClinicalTrials.gov (NCT06692075).

### EMS in Taipei metropolitan area

In response to emergency calls for OHCA events, the Taipei Metro EMS system proceeds with instant online dispatcher-assisted CPR by witnessed bystanders with or without a public automatic external defibrillator (AED) at the same time as EMS team dispatching. On arrival at the scene, the EMS team will perform ACLS, including high-quality chest compression, basic or advanced airway management, intravenous or intraosseous access establishment, or automated chest compression by the Lund University Cardiopulmonary Assist System, and AED defibrillations if needed, followed by intra-arrest escorted transportation with continuous telecommunication to emergency service of the Taipei Metro major disease emergency responsible hospitals in the Taipei Metro OHCA Total Care Consortium.

The Taipei metropolitan area has a densely distributed healthcare system. Based on recent data, the mean EMS response time (from emergency call to arrival at scene) is 6.4 ± 3.3 min, and the mean EMS transport time (from scene to ED arrival) is 4.5 ± 2.8 minutes [19]. Since the some buildings without elevator and the EMS had standard procedures to be performed on scene, and the area of New Taipei City is 7 times than Taipei City, we estimate the mean time from call to ED arrival approximately 40–60 min.

### Enrollment and randomization of trial population

Refractory OHCA is defined as cardiac arrest in patients transported to hospital with ongoing CPR. Upon receiving the EMS’s referral of OHCA patients, the OHCA response team, composed of emergency physicians, interventional cardiologists, and cardiac surgeons, will evaluate the eligibility of patients based on on-scene information. The inclusion and exclusion criteria are described in Table 1. When the patient arrives at the ED, a rapid screening is performed to reassure his/her eligibility. All eligible patients will be randomized into the emergency total extracorporeal life support (total ECLS) group and the standard advanced cardiac life support with rescue ECMO (**standard ACLS**) group (Fig. 1).

**Table 1 Tab1:** PreInclusion and exclusion criteria

Screening inclusion criteria	Pre randomization Exclusion	Post-randomization exclusions criteria
• Aged 18–75 years old	• Age under 18 or over 75	• Age < 18 years or > 75 years old
• Witnessed cardiac arrest with bystander cardiopulmonary resuscitation	• Major trauma	• Initial non-shockable rhythm, i.e. pulseless electrical activity or asystole
• Initial shockable rhythm, i.e. ventricular fibrillation or pulseless ventricular tachycardia	• Initial non-shockable rhythm	• Acute aortic dissection
• Need for repeated defibrillation shocks (> 2) by external defibrillator	• Major trauma	• Acute massive pulmonary embolism
• Estimated transportation time from activation of the emergency response system to arrival at emergency department of participant institutions less than 60 min	• Suicide, illicit drug overdose or intoxication	• Acute intracerebral hemorrhage
	• Pre-arrest mRS > 3 or CPC > 2	• Major trauma due to blunt, penetrating or burn injury
	• Unwitnessed CPR	• Severe peripheral artery disease
		• Known pregnancy
		• Suicide, illicit drug overdose or intoxication
		• Known pre-arrest mRS > 3 or CPC > 2
		• Active malignancy with a life expectancy of less than 1 year
		• Effective DNR order
		• Absolute contraindications to emergency coronary angiography, including known anaphylactic reaction to angiographic contrast media, acute bleeding

CPC, cerebral performance category; DNR, do-not-resuscitation; mRS, modified Rankin score

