**Fig. 1 Fig1:**
[figure not shown]
Study flowchart. Before arriving at ED, the eligibility of OHCA patients will be evaluated by the OHCA response team of the receiving hospital, based on on-scene information provided by EMS. For eligible OHCA patients, randomization will be completed within 5 min of arrival at ED. After CT imaging, patients of first enrollment will be checked again if any exclusion criteria are met. Only patients who received early coronary angiography and/or intervention will be included in the final analysis. ACLS: advanced cardiovascular life support; CCL: cardiac catheterization laboratory; CPC: cerebral performance category; CPR: cardiopulmonary resuscitation; CT: computed tomography; ECLS: extracorporeal life support; ED: emergency department; EKG: electrocardiography; EMS: emergency medical services; mRS: modified Rankin scale; OHCA: out-of-hospital cardiac arrest; ROSC: return of spontaneous circulation; ECG: echocardiography

Randomization is performed immediately upon ED arrival (target: within 5 min) for patients meeting inclusion criteria and experiencing refractory cardiac arrest (defined as ongoing CPR on arrival). Patients with stable ROSC before randomization (defined as sustained pulse with systolic BP ≥ 90 mmHg without ongoing chest compressions for ≥ 2 min) are not randomized and proceed directly to coronary angiography.

Patients with unstable ROSC defined as: (1) return of pulse but requiring ongoing chest compressions, (2) recurrent VF/VT requiring repeated defibrillation, (3) persistent profound hypotension with systolic BP < 90 mmHg or mean BP < 60 mmHg despite vasopressor support, or (4) intermittent epinephrine injection to maintain the heart beating are eligible for randomization."

A computerized randomization list is provided by the National Taiwan University Hospital Clinical Trial Center by a software app (REDCAP). The randomization is in 1:1 ratio, stratified by participant hospitals, with a permuted block of 4. In-hospital randomization is conducted by OHCA response team coordinators immediately after the eligible patients arrive at ED. The randomization codes will be maintained by the National Taiwan University Hospital Clinical Trial Center and monitored by the Data Safety Monitoring Committee. The EMS teams and intensivists in the cardiac intensive care unit (ICU) will be blinded to the study group assignment and follow the institutional standards for post-cardiac arrest care.

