#### Post resuscitation protocol

After initial stabilization at ED, electrocardiography and echocardiography would be arranged to identify cardiac causes for OHCA. Computed tomography would be arranged (either before or after cath intervention) to exclude non cardiac causes of OHCA or contraindication (Table 1). All patients without contraindications for coronary intervention will then be transferred to the cardiac catheterization laboratory (CCL) for coronary angiography. With successful emergent management, patients are admitted to the cardiac ICU for continued post-cardiac arrest care.

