#### Intervention—ECMO initiation

After randomization, if the enrolled patient has stable ROSC before initiating ECMO, he/she will be transferred to the cardiac catheterization laboratory (CCL) without ECMO support. The indications for ECMO include no ROSC or unstable ROSC (persistent or recurrent VF or pVT, profound cardiogenic shock with systolic blood pressure (BP) < 90 mmHg or mean BP < 60 mmHg despite intense inotropic support (bolus of epinephrine > 3 bolus), or persistent hypoxia with arterial oxygen saturation (SaO2) < 90% despite maximal ventilation support). The femoral artery and vein access will be cannulated under ultrasound guidance. ECMO would be deemed futile if more than one discontinuation criterion suggesting ineffective resuscitation (end-tidal carbon dioxide < 10 mmHg, partial pressure of oxygen in arterial blood < 50 mmHg or oxygen saturation < 85%, or serum lactate > 20 mmol/L) has been met.

However, if unstable ROSC persists as defined above, ECMO is initiated according to the randomization arm protocol. For the emergency total ECLS group (Fig. 1), the veno-arterial ECMO (VA-ECMO) will be initiated within 15 min after randomization. For standard ACLS with the recue ECMO group, patients will receive 15 min of ACLS at ED first. If there is no stable ROSC, the futility of ECLS would be reevaluated. Therefore, the recue VA-ECMO should be initiated after 15 min since randomization.

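### Table 1 lists several pre-existing conditions only as post-randomisation exclusions, so read literally a patient known on arrival to be ineligible can be randomised and started on ECMO before the re-check

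*Protocol article*

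**What the plan says.** All references are to the protocol article.

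- **Table 1 (Enrollment and randomization of trial population)** has one column of inclusion criteria and two of exclusions, before and after randomisation. Only the post-randomisation column contains "Effective DNR order", "Known pregnancy", "Active malignancy with a life expectancy of less than 1 year", "Severe peripheral artery disease" and "Absolute contraindications to emergency coronary angiography, including known anaphylactic reaction to angiographic contrast media, acute bleeding".
- **The text of the same section** refers to Table 1 for the criteria, describes a rapid screen on ED arrival to confirm eligibility, and says that eligible patients are randomised.
- **Fig. 1 legend and the text below it:** randomisation is targeted within 5 min of ED arrival, for patients who meet the inclusion criteria. The legend adds: "After CT imaging, patients of first enrollment will be checked again if any exclusion criteria are met".
- **Post resuscitation protocol:** "Computed tomography would be arranged (either before or after cath intervention"), following initial stabilisation. Only patients with no contraindication to coronary intervention go on to the catheterisation laboratory.
- **Intervention—ECMO initiation:** VA-ECMO in the total ECLS arm "will be initiated within 15 min after randomization".
- **Statistical analysis:** the primary analysis is by intention to treat in all enrolled patients.

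**The concern.** The five conditions exist before the arrest, and pregnancy and contrast anaphylaxis are worded as already known. None is a finding that only CT could produce. The trial treats each as disqualifying, yet its entry column omits them and its re-check comes late.

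Two things are at stake. First, patients whom the trial itself regards as ineligible may be enrolled, and in the total ECLS arm may start the trial intervention, although the disqualifying fact was available at the door. Second, each such patient creates an avoidable problem for the analysis of an open-label trial. Either the patient stays in the intention-to-treat set and blurs the contrast, or the patient is removed once the allocation is known.

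**Working it through.** **Step 1. Compare the two exclusion columns.**

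| Condition | Before randomisation | After randomisation |
|---|---|---|
| Age, rhythm, major trauma, suicide/overdose/intoxication, pre-arrest mRS or CPC | yes | yes |
| Unwitnessed arrest | yes | no |
| Aortic dissection, massive pulmonary embolism, intracerebral haemorrhage | no | yes |
| DNR order, pregnancy, short-prognosis malignancy, severe peripheral artery disease, contraindication to angiography (including known contrast anaphylaxis) | no | yes |

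The third row plausibly needs imaging, so its place is understandable. The fourth row is mainly history. Difficulty in taking a history does not explain its absence from the first column, because pre-arrest mRS/CPC is history too and is listed twice. The table thus uses double listing where a condition is to be checked at both steps.

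**Step 2. Put the events in order (total ECLS arm).**

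- ED arrival: 0 min.
- Randomisation: by about 5 min (target).
- ECMO start: by about 5 + 15 = 20 min.
- Exclusion re-check: after CT, for which no time is fixed and which may come after the catheter procedure.

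ECMO can therefore precede the re-check. Rescue ECMO in the other arm, after 15 min of ACLS, could also precede CT, but the point is most direct for the total ECLS arm.

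**Step 3. Size, as an illustration only.** Stated inputs (Sample size rationale): 25% versus 12%, two-sided 5% chi-square test, 80% power, 10% dropout, 186 per arm.

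The plan's own figure does not reproduce. The pooled-variance formula gives

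n = [1.96 √(2 × 0.185 × 0.815) + 0.842 √(0.25 × 0.75 + 0.12 × 0.88)]² / 0.13² = 139 per arm,

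and 139 / 0.90 = 155 with dropout. The figure 186 equals the 90%-power size before dropout. That mismatch is a separate matter and this point does not depend on it. I take 186 as given.

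Power = Φ[(d − 1.96 s₀) / s₁], where d is the difference in proportions, s₀ = √(2 p̄(1 − p̄)/n) with p̄ the mean of the two rates, and s₁ = √((p₁(1 − p₁) + p₂(1 − p₂))/n). At n = 186 and 25% versus 12%: s₀ = 0.04026, s₁ = 0.03970, and (0.13 − 0.07892)/0.03970 = 1.287, so power is 90.1%.

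Let a share f of randomised patients have such a condition, and assume that none of them reaches CPC 1–2. Both rates are then multiplied by (1 − f):

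| f (assumed) | Rates | Power, 186 per arm | Power, 167 per arm (186 × 0.90) |
|---|---|---|---|
| 0% | 25.0% vs 12.0% | 90.1% | 86.8% |
| 5% | 23.8% vs 11.4% | 88.2% | 84.6% |
| 10% | 22.5% vs 10.8% | 86.0% | 82.2% |
| 20% | 20.0% vs 9.6% | 80.9% | 76.5% |

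Zero favourable outcomes is the worst case for these patients' outcomes, but not the lowest power possible. If they instead had 12% in both arms, power at 186 per arm would be 87.4%, 84.1% and 75.9% for 5%, 10% and 20%.

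**The case against.** The strongest reply is that the prose already provides a wider screen. The section refers to Table 1 as a whole, says that eligibility is confirmed on arrival and that eligible patients are randomised. The Fig. 1 legend speaks of patients being checked again, which implies an earlier check. On that reading the post-randomisation column is simply the full list for the second look. This reading is possible, and it is why the point is one of conflicting passages, not of an instruction to enrol such patients. It does not settle the matter, because it sets aside the column heading and the double listing of other items. If it is what the sponsor means, the table still needs the same correction.

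Three further objections stand in part or in full:

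- A reader might infer that a patient with known contrast anaphylaxis could have angiography before the exclusion is applied. The documents do not support this, because the post-resuscitation section sends only patients without contraindications to the catheterisation laboratory. Nor does any passage tell staff to cannulate a patient with a known DNR order; the gap is that the table does not screen for it first.
- Severe peripheral artery disease and a malignancy prognosis may not be knowable within 5 min of arrival under ongoing CPR. A later check for history that surfaces late is a defensible choice. It is no reason to omit a condition that is already known.
- A reader might turn an assumed 10% prevalence into about 37 of 372 patients randomised in error. The documents give no prevalence, and pregnancy or contrast allergy does not by definition rule out a good neurological outcome, so such a count is not a finding.

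The article is condensed and the flowchart is not shown. The table is also loosely drafted (major trauma appears twice before randomisation), which weakens inference from an omission but is itself a reason to correct it.

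**Conclusion.** The point holds as an inconsistency between Table 1 and the screening text, with a practical consequence. Followed literally, the table lets a patient known on arrival to have one of the five conditions be randomised, and in the total ECLS arm put on ECMO, before the exclusion is applied. It concerns randomisation and ECMO start, not angiography.

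The effect on power is unknown. The fall from 90.1% to between 88.2% and 80.9% at 186 per arm rests on an assumed 5% to 20% prevalence with no favourable outcomes, neither of which comes from the documents. At low prevalence the loss is modest. The case rests on not randomising patients already known to be ineligible, and on not creating avoidable exclusions after allocation in an open-label trial.

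**What to change.** 1. In Table 1, list the effective DNR order, pregnancy, active malignancy with life expectancy under 1 year, severe peripheral artery disease and contrast anaphylaxis in the pre-randomisation column as well, each qualified as known at ED arrival.
2. State in the enrolment text that the existing rapid screen covers these items on the information then available, so that the text, Table 1 and the Fig. 1 legend agree.
3. State that a condition discovered only after randomisation does not remove the patient from the intention-to-treat set. The Fig. 1 legend, which limits the final analysis to patients who had early angiography and/or intervention, must be reconciled with this.

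The cost is an amendment to one table, a sentence or two of text and a few tick-boxes on the screening form. No procedure is added. Some patients who are ineligible under the trial's own criteria would no longer be randomised.

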**Fig. 1 Fig1:**
[figure not shown]
Study flowchart. Before arriving at ED, the eligibility of OHCA patients will be evaluated by the OHCA response team of the receiving hospital, based on on-scene information provided by EMS. For eligible OHCA patients, randomization will be completed within 5 min of arrival at ED. After CT imaging, patients of first enrollment will be checked again if any exclusion criteria are met. Only patients who received early coronary angiography and/or intervention will be included in the final analysis. ACLS: advanced cardiovascular life support; CCL: cardiac catheterization laboratory; CPC: cerebral performance category; CPR: cardiopulmonary resuscitation; CT: computed tomography; ECLS: extracorporeal life support; ED: emergency department; EKG: electrocardiography; EMS: emergency medical services; mRS: modified Rankin scale; OHCA: out-of-hospital cardiac arrest; ROSC: return of spontaneous circulation; ECG: echocardiography

Randomization is performed immediately upon ED arrival (target: within 5 min) for patients meeting inclusion criteria and experiencing refractory cardiac arrest (defined as ongoing CPR on arrival). Patients with stable ROSC before randomization (defined as sustained pulse with systolic BP ≥ 90 mmHg without ongoing chest compressions for ≥ 2 min) are not randomized and proceed directly to coronary angiography.

Patients with unstable ROSC defined as: (1) return of pulse but requiring ongoing chest compressions, (2) recurrent VF/VT requiring repeated defibrillation, (3) persistent profound hypotension with systolic BP < 90 mmHg or mean BP < 60 mmHg despite vasopressor support, or (4) intermittent epinephrine injection to maintain the heart beating are eligible for randomization."

A computerized randomization list is provided by the National Taiwan University Hospital Clinical Trial Center by a software app (REDCAP). The randomization is in 1:1 ratio, stratified by participant hospitals, with a permuted block of 4. In-hospital randomization is conducted by OHCA response team coordinators immediately after the eligible patients arrive at ED. The randomization codes will be maintained by the National Taiwan University Hospital Clinical Trial Center and monitored by the Data Safety Monitoring Committee. The EMS teams and intensivists in the cardiac intensive care unit (ICU) will be blinded to the study group assignment and follow the institutional standards for post-cardiac arrest care.

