### Statistical analysis

#### Sample size rationale

The trial is designed to demonstrate a treatment effect on the primary endpoint. Accepting a power of 80% and a level of significance of 5%, the sample size is calculated using a two-sided chi-square test. In reference to published multicenter trials, we estimate a 30-day neurologically favorable survival of 25% and 12% in the emergency total ECLS group and the standard ACLS with rescue ECMO group, respectively. Assuming a 10% dropout rate, we plan to enroll 186 participants per arm (roughly 200). No interim analysis is planned. If interim analysis is deemed necessary determined by Consortium committee, we will conduct one interim analysis 1 year after enrollment, and the statistical testing will be adjusted to this accordingly. The flowchart of intention to treatment and per protocol are attached in supplement.

All patients enrolled in the study will be analyzed primarily on an intention-to-treat basis. Continuous variables will be reported as mean ± standard deviation or median with interquartile range. Categorical variables will be presented as frequency. A logistic regression model with the stratification variable (center) will be conducted to evaluate the primary efficacy endpoint by treatment group. Odds ratios are to be calculated as effect estimates with 95% confidence intervals. Patients whose primary outcome cannot be assessed will be regarded as failures.

Per-protocol analysis, which only includes patients who adhere to the allocated protocol, will be performed to minimize the impact of non-adherence or deviations from the strict protocol.

For patients randomized to the total ECLS group, if ECPR is not required due to stable ROSC at ED or ECMO is initiated after 20 min since arriving at ED or after 60 min since emergency calls, they would be excluded from per-protocol analysis. Similarly, for patients randomized to the standard ACLS with rescue ECMO group, if ECMO is initiated within 20 min of arriving at the ED or within 60 min of emergency calls, they would be considered crossover and excluded from per-protocol analysis.

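### Exclusions after randomisation, and an angiography-only final analysis, conflict with intention-to-treat and can bias the comparison in either direction

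*Protocol article*

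**What the plan says.** All references are to the protocol article.

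- **Timing of randomisation.** The Fig. 1 caption says that "randomization will be completed within 5 min of arrival at ED".
- **Exclusions after that point.** The third column of Table 1 is headed "Post-randomization exclusions criteria" and has 13 entries. They include "Acute intracerebral hemorrhage" and "Absolute contraindications to emergency coronary angiography, including known anaphylactic reaction to angiographic contrast media, acute bleeding".
- **When they are applied.** The Fig. 1 caption states: "After CT imaging, patients of first enrollment will be checked again if any exclusion criteria are met". Its next sentence limits the final analysis to patients who had early coronary angiography, intervention or both.
- **When CT happens.** The section Post resuscitation protocol allows CT on either side of the catheterisation procedure.
- **When treatment starts.** Under Intervention—ECMO initiation, in the emergency total ECLS arm "the veno-arterial ECMO (VA-ECMO) will be initiated within 15 min after randomization". The section on ECMO management specifies heparin and names bleeding among the complications.
- **Analysis principle.** The section headed Sample size rationale, which also holds the analysis text, states: "All patients enrolled in the study will be analyzed primarily on an intention-to-treat basis". It counts patients whose primary outcome cannot be assessed as failures, and refers to a supplement for the intention-to-treat and per-protocol flowcharts.

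**The concern.** Randomisation protects the comparison only if membership of the analysis set cannot depend on what happens after allocation. Here it can, in three ways.

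1. **Who reaches the check.** A CT finding can exclude only a patient who gets as far as CT, and the caption's last restriction keeps only patients who get as far as angiography. One arm is to receive ECMO within 15 minutes, while the other first receives 15 minutes of ACLS. Allocation can therefore change who reaches either point.
2. **Whether the excluding event occurs.** The check can come after cannulation, anticoagulation and catheterisation. Table 1 uses the word known for pregnancy, pre-arrest function and contrast anaphylaxis. It does not do so for intracerebral haemorrhage, acute bleeding or severe peripheral artery disease. As worded, a haemorrhage that begins after allocation can meet the criterion.
3. **Who judges.** The trial is open-label. The article describes blinding for the EMS teams, the cardiac ICU intensivists and the neurologists who score the outcome. It describes none for the exclusion check.

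At stake are the population of the primary analysis and possibly the safety data. Serious adverse events related to ECMO and angiography are safety endpoints, and some bleeding events could be lost if excluded patients also leave the safety set.

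**Working it through.** **Plan's own figures.** The article gives no rate of post-randomisation exclusion, so there is no figure to reproduce on this point. It does give favourable-outcome rates of 25% and 12% and 186 patients per arm. The stated inputs (two-sided 5%, 80% power) yield 139 per arm, or 139/0.90 = 155 with 10% dropout, and not 186. That is a separate matter; 186 serves below only as the number randomised per arm.

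**Formula.** If a fraction f of an arm is removed and all of those removed are failures, a true rate p is reported as p/(1 − f).

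**Assumptions (none from the documents).** No true effect is set at p = (25% + 12%)/2 = 18.5% in both arms.

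- *Reading A, CT exclusions only.* 10% have a CT-detectable exclusion; 85% (ECLS) and 60% (standard ACLS) reach CT; treatment-related bleeding removes a further 5% and 2%. Then f = 0.10 × 0.85 + 0.05 = 13.5% and 0.10 × 0.60 + 0.02 = 8.0%.
- *Reading B, angiography-only set.* 85% and 60% reach angiography and the rest are failures. Then f = 15% and 40%.
- *Equal exclusion.* f = (13.5% + 8.0%)/2 = 10.75% in both arms.
- *All randomised analysed.* f = 0 in both arms.

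| Case | No true effect, ECLS vs standard | Planned 25% vs 12% |
|---|---|---|
| All randomised | 18.5% vs 18.5%, 0 points | 13.0 points |
| Equal exclusion | 20.7% vs 20.7%, 0 points | 13.0/0.8925 = 14.6 points |
| Reading A | 0.185/0.865 = 21.4% vs 0.185/0.92 = 20.1%, +1.3 points | 28.9% − 13.0% = 15.9 points |
| Reading B | 0.185/0.85 = 21.8% vs 0.185/0.60 = 30.8%, −9.1 points | 29.4% − 20.0% = 9.4 points |

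If the arms are swapped in Reading A (8.0% vs 13.5% removed), the null difference becomes −1.3 points.

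**False-positive rate.** Let d be the reported difference, with arm sizes 186(1 − f), se0 the pooled and se1 the unpooled standard error. The chance of rejecting at two-sided 5% is Φ((d − 1.96·se0)/se1) + Φ((−d − 1.96·se0)/se1).

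- Reading A: d = 0.0128, se0 = se1 = 0.0445, giving 4.7% + 1.2% = 6.0% after rounding; odds ratio 1.08.
- Reading B: d = −0.0907, se0 = 0.0539, se1 = 0.0547, giving 39%, almost all of it against ECLS; odds ratio 0.62.
- Equal exclusion: 5.0%; odds ratio 1.00.

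Across p from 12% to 25%, removing 10% vs 5% gives odds ratios of 1.06 to 1.08 and false-positive rates of 5.4% to 6.1%. Removing 15% vs 5% gives 1.14 to 1.17 and 6.9% to 9.7%.

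**The case against.** **The intention-to-treat sentence may govern.** If every randomised patient is analysed, f = 0 and there is no bias. The flowcharts in the supplement, which is not shown, may say so. This stands as a possibility, but the sentence speaks of enrolled patients and does not say whether someone excluded after randomisation still counts as enrolled. Even if the supplement keeps everyone, Table 1 and the caption contradict it.

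**The criteria are mostly baseline facts.** Age, initial rhythm, pregnancy and pre-arrest function are fixed before allocation. The stated purpose of CT is to find non-cardiac causes or contraindications, so intracerebral haemorrhage is most naturally read as a cause of the arrest. Acute bleeding is given as an example of a contraindication to angiography, and a bleed caused by angiography fits that poorly. This largely stands: the article does not set out to exclude treatment complications. The defect is that it does not limit these criteria to conditions present before randomisation.

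**A reader might infer that the exclusions inflate the benefit of ECLS.** The documents do not support a direction. Standard-arm patients can also receive rescue ECMO, and angiography is planned in both arms. An account in which early deaths stay in as failures ignores the caption's angiography restriction, under which those deaths leave, and the same 85% and 60% then work against ECLS. Much of the rise from 13.0 to 15.9 points in Reading A is also plain rescaling, since equal exclusion alone gives 14.6.

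**A reader might also infer that bleeding harms will be dropped.** No passage removes excluded patients from safety reporting, and ECMO complications are to be recorded on the case report form. The loss is possible, not shown.

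**Conclusion.** The point holds as a contradiction over who is analysed. Table 1 and the Fig. 1 caption remove patients after randomisation, on checks that can follow the allocated treatment, while the analysis text promises intention-to-treat. It has to be resolved before analysis because it determines the primary analysis population.

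The bias is possible, and the documents establish neither its size nor its direction. It requires unequal removal between arms. Under the assumptions shown, a true null is reported as anything from 1.3 points in favour of ECLS to 9.1 points against it, and equal removal produces no false difference. The percentages reaching CT or angiography and the exclusion rates are all assumed, as is the premise that everyone removed is a failure.

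**What to change.** Reconcile Table 1, the Fig. 1 caption, the section Post resuscitation protocol and the Statistical analysis section as follows.

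1. State that every randomised patient stays in the primary intention-to-treat analysis and in the safety analysis, whatever is found after allocation.
2. Delete the angiography-only restriction from the primary analysis.
3. If an analysis confined to cardiac causes is wanted, make it a sensitivity analysis. Limit its exclusions to conditions present before randomisation, adjudicated by people unaware of arm and outcome.

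The cost is wording in the article and in the analysis plan, plus blinded adjudication if the sensitivity analysis is kept. The small downside is that some non-cardiac arrests remain in the denominator and slightly dilute the effect.
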